### Laboratory testing and sample handling

We are performing laboratory tests after the enrolment of a child in the study that includes blood for haemoglobin percentage, total and differential counts of white cell count (WCC), haematocrit, blood culture and antimicrobial susceptibility of pathogens, serum electrolytes and creatinine, calcium and magnesium, serum bilirubin, serum lactate, C reactive protein, procalcitonin and cardiac troponin I, stool (rectal swab for cholera, Salmonella, Shigella and Campylobacter) and urine culture, chest radiograph, and arterial or capillary blood gas analysis. We are also doing a test for the exclusion of dengue during the dengue prevalent period in the country. We are checking serum lactate at enrolment and 4–6 hours after enrolment. Our target is to send samples for laboratory tests within 30 min to 1 hour of enrolment. When a child is in shock, very often it is difficult to get an adequate amount of blood for proposed testing. Then we prioritise tests based on clinical relevance. We are doing the blood grouping, screening and cross-matching while we are following a child for study eligibility. We are performing cardiac ultrasonography during screening, enrolment and 4–6 hours later after enrolment. As we are enrolling children 24×7, the study physicians are doing the bedside cardiac ultrasound and storing the images of specific preselected parameters. Later the images are reviewed by experienced cardiologists to get the measurements.

We are archiving blood samples and planning to check serum leptin at the end of the study.

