### Trial design

This is a randomised, three-arm, controlled, non-masked clinical trial in children 1–59 months old with SAM or severely underweight and shock (figure 1). With parental written informed consent, children are allocated to the study interventions following randomisation, in addition to usual supportive care that includes broad-spectrum antibiotics, oxygen inhalation, intravenous glucose, etc. The study protocol follows the Standard Protocol Items: Recommendations for Interventional Trials guidance for protocol reporting (modified to reflect the ongoing study activities)^18^ (table 1).

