### Outcome measures

Primary outcome variable is the case fatality rate (at 28±3 days from the day of enrolment). The secondary outcome variables are the rate of treatment failure, rate of MAP stabilisation at 48 hours after enrolment, need for mechanical ventilation, the incidence of heart failure, duration of ICU stay and total hospitalisation, time-to-achieve recovery, evaluation of cardiac function by POC ultrasonogram (right ventricular function, left ventricular function and IVC collapsibility).

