### Protocol amendments

After the first approval of the protocol, we included two cardiologists as coinvestigators. After 1 year of enrolment, we made a change in the inclusion criteria also. Now we are including severely underweight children along with SAM children. So, we required amendments to the protocol which were all reviewed and approved by the icddr, b IRB. Now we are using version 2.2 of the protocol.

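### The ultrasound outcomes are measured later from stored images, where masking to arm is feasible, yet the trial is declared non-masked with no exception for the readers

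*Protocol article*

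**What the plan says.** All references are to the protocol article.

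- **Masking.** Trial design describes a "randomised, three-arm, controlled, non-masked clinical trial", and the Abstract says the same. Neither place sets image readers or any other assessor apart.
- **Outcome.** Outcome measures lists among the secondary outcomes "evaluation of cardiac function by POC ultrasonogram (right ventricular function, left ventricular function and IVC collapsibility".
- **Acquisition.** Under Laboratory testing and sample handling, "the study physicians are doing the bedside cardiac ultrasound and storing the images of specific preselected parameters".
- **Measurement.** The same section continues: "Later the images are reviewed by experienced cardiologists to get the measurements". It does not say what information accompanies the images.
- **Timing.** "We are performing cardiac ultrasonography during screening, enrolment and 4–6 hours later after enrolment". Table 1 places the enrolment scan at hour 0 and allows a further scan during the hospital course if required.
- **Cardiologists on the team.** Protocol amendments reports that "we included two cardiologists as coinvestigators". It does not say that they are the readers.

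**The concern.** Ventricular function and IVC collapsibility depend on where a reader places measurements on an image. A reader who knows whether a child received an inotrope or blood can be influenced, without intending it, by what that treatment is expected to do. The Introduction supplies such an expectation, since it presents inotropes as the better option when shock comes from myocardial dysfunction or vasoregulatory failure.

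The trial also gives these measurements weight. Bedside cardiac evaluation is listed among its strengths, and the Introduction expects ultrasound to help separate fluid deficit from cardiac dysfunction. If the arms differed in cardiac function after treatment, a critic could put the difference down to the readers, and the article describes no safeguard with which to answer.

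The workflow already separates the person who scans from the person who measures. That is the difficult part of masked reading, and it is in place. What is not stated is that the files reach the readers without the arm.

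**Working it through.** **1. Who could know the arm, and at which scan**

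| Scan | Position relative to allocation | Room for reader bias between arms |
|---|---|---|
| Screening | Before randomisation | None from treatment; a later reader told the arm could still be influenced, but the true arms are comparable |
| Enrolment, hour 0 | At allocation, before treatment has had time to act | Small |
| 4–6 hours after enrolment | After allocation and during or after treatment | Main exposure |
| Later, if required | After allocation | Exposed |

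At 4–6 hours many children in the inotrope arms may still be on the infusion, because Study intervention and procedure has the dose continued for 6 hours once the goal is reached. This is the scan at which an expected treatment effect would be looked for.

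**2. Whether the reason for not masking applies to the reading**

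Arm C is a transfusion over 3 hours; arms A and B are syringe-pump infusions adjusted at 15-minute steps. Bedside staff cannot be masked to that difference. The reader works later, from files, so the constraint ends when the image is stored.

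**3. What is not touched**

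"Primary outcome variable is the case fatality rate (at 28±3 days from the day of enrolment"). Death is not read from an image. The sample size is built on death alone: with 61% versus 31%, two-sided alpha 0.05, 80% power and unpooled variance,

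n = (1.96 + 0.84)² × (0.61×0.39 + 0.31×0.69) / 0.30² ≈ 40 per group.

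Then 40/0.9 gives 45 after rounding up, and 3 × 45 = 135, as the article states. Masked reading would change none of these figures.

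**4. What a reader shift would do, if there were one**

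The documents contain no reader-error figure, so the shifts below are assumptions. Take no true difference, a systematic shift of d SD in one arm, n children measured per arm, and a two-sided 5% z-test between that arm and another.

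- Noncentrality: δ = d × √(n/2)
- Rejection probability: P(Z > 1.96 − δ) + P(Z < −1.96 − δ)

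For n = 40, √20 = 4.472:

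- d = 0.20: δ = 0.894; 0.143 + 0.002, about 14.5%
- d = 0.25: δ = 1.118; 0.200 + 0.001, about 20%

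Some children will die or have no usable scan by then, and the analysis section plans a three-group test first. Taking 30 measured per arm (an assumption) gives:

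| Shift in one arm | Pairwise z-test, n = 40 | Pairwise z-test, n = 30 | Three-arm F-test, n = 30 |
|---|---|---|---|
| 0.20 SD | 14.5% | 12% | 11% |
| 0.25 SD | 20% | 16% | 15% |

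Under these assumed shifts the error rate is two to four times the nominal 5%. The table shows what bias would do if present; it is no evidence that any is present.

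**The case against.** The strongest objection is that the article never says the readers are unmasked. The label non-masked may describe only how treatment is given, and open-label trials can have masked image reading. The article also condenses a full protocol, version 2.2, which is not shown and which may set out coding and reading procedures.

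This stands as far as it goes. A reader might infer that the cardiologists know each child's arm; the text does not support that. A reader might also infer that the two coinvestigator cardiologists are the people who read the images. That is plausible, but the article does not say so, the argument does not need it, and being a coinvestigator would not by itself show knowledge of the allocation.

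The objection does not remove the point. The article does more than stay silent on a detail: it states the masking status of the trial without qualification, and it describes who acquires, who measures and when. Together these leave the measurement with no stated protection at the one step where protection is easy.

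Three further limits are fair. The aim of telling fluid deficit from cardiac dysfunction rests largely on scans before treatment, where knowledge of the arm matters little. Physicians who know the arm still acquire and store the later images, so masked reading removes only part of the possible bias. And the false-positive figures rest on shifts chosen for illustration.

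**Conclusion.** The point holds as a low-cost improvement to a secondary outcome. The trial is declared non-masked without exception, while the ultrasound measurements are made in a setting where masking to arm is feasible. Nothing stated in the article prevents the readers from knowing the allocation. Reader bias is neither shown nor quantified by the documents.

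The scope is the scan at 4–6 hours and any later scan, for ventricular function and IVC collapsibility. The primary outcome, the sample size and the power are untouched. The rates of about 14.5% and 20% depend on assumed shifts of 0.20 and 0.25 SD in one arm, 40 measured children per arm and a pairwise test, and should not be cited as an estimate of what will happen in this trial.

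**What to change.** State in the protocol that:

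1. Stored images are stripped of identifiers and treatment arm, and given a study code.
2. The same cardiologists measure them masked to allocation.
3. The arm is linked only after the measurements are locked.
4. Any post-randomisation image already read with the arm known is read again in this way.
5. Bedside acquisition remains unmasked, and this is acknowledged as a limitation of the ultrasound outcomes.

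If the full protocol already provides for masked reading, one sentence saying so is enough, with the non-masked label qualified accordingly.

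The cost is a little file coding and possibly a short re-read. Study status gives 18 children enrolled by August 2022, so the backlog at that date was small; the number read since then is not stated. No new procedure, reader or patient is needed, and patient care does not change.

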### Study intervention and procedure

This is a three-arm trial where the intervention arms (dopamine and epinephrine) will be compared with the WHO standard intervention (blood transfusion). All study children stay at ICU for close monitoring.

During the screening, children receive intravenous isotonic fluid @ of 15 mL/kg over 1 hour (maximum two boluses, ie, up to 30 mL/kg) as per WHO standard of care. The choice of isotonic fluid is Ringer’s lactate/Hartsol (normal saline if any suspicion of hyperkelaemia, acetate if severe dehydration is predominant). Dextrose is added if a child has hypoglycaemia with a random blood sugar <3 mmol/L. The study team members work to assess the eligibility and discuss with the parents/caregiver for possible enrolment. The regular ICU team helps in patient care. At the end of the screening, if the fluid refractory shock is diagnosed, then the study team proceed with written consent to avert the gap between consent to starting appropriate management of the child.

Children with fluid refractory shock are randomised to blood transfusion, dopamine or epinephrine therapy. Children in the dopamine arm (treatment category A) receive dopamine, 8 μg/kg/min (increasing the dose after 15 min to 12 μg/kg/min to a maximum of 15 μg/kg/min, up to the achievement of goal). Children in the epinephrine arm (treatment category B) receive epinephrine, 0.1 μg/kg/min (increasing the dose after 15 min to 0.2 μg/kg/min to a maximum of 0.3 μg/kg/min, up to the achievement of goal). We are using peripheral lines to give dopamine or epinephrine. Drugs are prepared as intravenous infusion and instilled by an infusion/syringe pump. Children in the blood transfusion arm (treatment category C) receive a transfusion of whole human blood at a dose of 10 mL/kg over 3 hours (figure 1). To arrange blood within the time frame, we have an institutional volunteer donor list, two medical technologists dedicatedly work for this study, and we are also excluding children having negative blood groups. Even after that, If blood could not be arranged within 1 hour after the event of fluid refractory shock, we will start rescue therapy considering the event as treatment failure. In addition to the study interventions, broad-spectrum antibiotic therapy, oxygen therapy and frequent monitoring, all children receive intravenous maintenance fluids with half-strength normal saline and 5% dextrose @ of 3 mL per kg per hour during the arrangement of blood transfusion and intervention with inotropes. Along with maintenance fluid, we add intravenous fluid if diarrhoea continues or a child develops dehydration. Intravenous fluid maintenance is continued for 6 hours after the achievement of a goal and is further continued if the goal is not achieved. Our goal is to achieve MAP>50 mm Hg and/or urine output ≥1 mL/kg per hour. After randomisation, we monitor children at every 15 min interval during the intervention to assess mental status by using AVPU, an acronym from ‘alert, verbal, pain, unresponsive’, capillary refill time, rate and volume of the radial pulse, cold/warm extremities, urine output, blood pressure, respiratory rate, peripheral capillary O_2_ saturation and features of heart failure. We measure BP manually using the standard cuff. To minimise the use of a catheter, we apply a paediatric urine collector bag and measure the urine output. However, for a female child, it is difficult to measure. We are considering an indwelling catheter if required. Mechanical ventilation is provided if the child did not respond to bubble CPAP (if SpO2<85% at least after an hour of bubble CPAP oxygen therapy) or had a respiratory failure (pH<7.2 and Partial pressure of carbon dioxide (PCO_2_)>60 mm Hg in ABG analysis or Oxygen saturation to fraction of inspired oxygen ratio (SpO_2_/FiO_2_)<265). Children who develop complications such as acute abdomen not responding to conservative management or acute renal insufficiency requiring dialysis are referred to a suitable higher facility for proper management. At the achievement of the goal, we continue the dose of dopamine or epinephrine for 6 hours. We follow up with the child every 30 min to 1-hour interval. Thereafter, we reduce the dose in a stepwise manner similar to how we increased the dose. If the child becomes hypotensive again, we reintroduce the previous dose and follow the same procedure for further iteration.

### Rescue therapy

The failure of any intervention is declared as a treatment failure. Then for children in the dopamine and blood transfusion arm, we start epinephrine as rescue therapy in a stepwise manner starting from 0.1 μg/kg/min and increasing every 15 min by 0.1 μg/kg/min up to restoration of the desired goal (MAP>50 mm Hg or urine output >1 mL/kg/hour) and the highest dose is 0.5 μg/kg/min (or consultant discretion) For children in the epinephrine arm, the dose is increased every 15 min from 0.3 μg/kg/min (the highest proposed intervention dose) to a max of 0.5 μg/kg/min. On achieving the goal, we continue the same dose for 4–6 hours and then we de-escalate in a stepwise manner.

If the goal is not achieved with injection of epinephrine then injection of norepinephrine is [contact] μg/kg/min and we increase the dose every 15 min by 0.1 μg/kg up to restoration of the desired goal (MAP>50 mm Hg or urine output >1 mL/kg/hour) and the highest dose is 0.5 μg/kg/min. On achieving the goal, we continue the same dose for 6 hours and then will de-escalate in a stepwise manner. For those patients whose MAP is not restored with inotropes, injection hydrocortisone @ 2 mg/kg every 6 hours is added.^19^ During rescue therapy, for doses and selection of any inotrope(s), we are following the recommendation from the Paediatric intensive care unit (PICU) consultant as all cases are not the same.

### Feeding and other care

Depending on the clinical condition either we keep the child NPO (nothing per oral) or start trophic feeding for children who had MAP>50 mm Hg and had no evidence of paralytic ileus. Feeds consist of ‘Milk Suzi’ (similar to WHO-recommended F-75) for children older than 6 months, and modified infant formula (in addition to breast milk, if applicable) is given to infants 1–6 months of age.^20^ Thus, we provide a fluid volume of 120 mL/kg/day to deliver 80–82 kcal/kg/day. A child is kept warm to prevent hypothermia. If there is hypoglycaemia (random blood glucose <3 mmol/L), correction is given with 10% glucose intravenously in a dose of 5 mL/kg to be followed by 10% glucose administration through a nasogastric tube, following the standard protocol of the hospital.

### Nutritional rehabilitation

As the study children have SAM, they require nutritional rehabilitation. After recovering from acute illness, the mothers/caregivers are asked to stay in the hospital’s nutritional rehabilitation unit (NRU) for 2–3 weeks. In the NRU, the standard dietary protocol is followed for nutritional rehabilitation and the children are discharged on fulfilling discharge criteria.

### Postdischarge follow-up

We follow up with a child on the 28th day (±3 days) of enrolment to know their clinical status over the phone. In addition, the children who were discharged from NRU or taking early discharge from the ward, are requested to come for a prescheduled follow-up at the hospital nutrition follow-up unit (NFU) of icddr, b. We followed the children at NFU and record their nutritional status and health problems. Our scheduled follow-ups for this study children are in two time points; once after 7 days of discharge, then after 15 days of first follow-up. If any mother/caregiver fails to attend a follow-up visit, then we communicate with the mother/caregiver over the phone for two time points. We document the outcome whether they are alive or not, and had any intercurrent illness, for example, diarrhoea, pneumonia.

### Outcome measures

Primary outcome variable is the case fatality rate (at 28±3 days from the day of enrolment). The secondary outcome variables are the rate of treatment failure, rate of MAP stabilisation at 48 hours after enrolment, need for mechanical ventilation, the incidence of heart failure, duration of ICU stay and total hospitalisation, time-to-achieve recovery, evaluation of cardiac function by POC ultrasonogram (right ventricular function, left ventricular function and IVC collapsibility).

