**Figure 1 F1:**
[figure not shown]
Study flow chart showing the procedures of screening and enrolment and allocation of a child in any of the three treatment categories and ways of rescue therapy if the study goal is not achieved. Hb, haemoglobin: WAZ, weight for age.

**Table 1 T1:** Standard Protocol Items: Recommendation for Interventional Trials (SPIRIT) Figure. The schedule of enrolment, interventions, and assessments.

Indicators	Screening	Study period						
		Enrolment and allocation	Study drugs administration and F-U	Rescue therapy	Hosp course up to disposal	Follow-up after discharge		
						1st follow-up	2nd follow-up	28th follow-up (over phone)
Time point	Day 0	Hour 0	Hour 0–3 (1 hour for dopamine and epinephrine, 3 hours for Blood)	Hour 1—disposal (for dopamine and epinephrine) Hour 3—disposal (for blood)		Day 7±2	Day 21±2	Day 28±3
Enrolment:								
Eligibility screen	x							
Informed consent	x	x						
Randomisation and allocation		x	X					
Interventions:								
Different drugs (dopamine or epinephrine or blood)			X					
Assessments:								
Demographic		x						
Comorbidities		x						
Physical examination	x	x	X	x	x	x	x	–
Primary outcome:								
Case fatality								x
Secondary outcomes:								
Treatment failure			X					
MAP stabilisation at 48 hours after enrolment				x	x			
Mechanical ventilation			X	x	x			
Incidence of heart failure			X	x	x			
Duration of ICU stay					x			
Duration of total hospitalisation					x			
Time-to-achieve recovery from shock			X	x	x			
Ventricular function by cardiac USG	x	x		x	x (If require)			
IVC collapsibility	x	x		x	x (If require)			
*Detection of leptin from stored blood		x						

*According to the addendum (ERC approval on 21 October 2021), at the end of the study, stored blood samples will be tested for leptin.

F-U, follow-up; ICU, intensive care unit; IVC, inferior vena cava; MAP, mean arterial pressure; USG, ultrasonography.

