##### Inclusion criteria

Inclusion criteria are children aged 1–59 months of either sex having diarrhoea and SAM who develop fluid refractory shock either at admission or at any point during their treatment in the hospital (which might be due to cholera or other dehydrating diarrhoea or severe sepsis). We also included children having severe underweight as they are also vulnerable and their mortality rate is also high. We are using corrected weight for the anticipated loss of fluids to calculate SAM or severe underweight.

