##### Exclusion criteria

Exclusion criteria are severe anaemia (haemoglobin (Hb) <5 g/dL) and sclerema where blood transfusion is a mandate, congenital anomalies (tetralogy of Fallot, TOF)/atrial or ventricular septal defect (trisomy 21, etc), negative blood groups, a requirement of cardiopulmonary resuscitation during screening and non-consent from the caregivers/parents.

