Information is also collected about each child’s feeding practice, which included their history of breastfeeding, formula feedings, or alternative complementary feedings, and also immunisation status. Data on clinical examination findings are recorded by the study physician and include pulse, respiratory rate, axillary temperature, anthropometric measurements (ie, height, weight, mid-upper arm circumference (MUAC) for calculation of Z score), chest auscultation, oxygen saturation, presence or absence of chest wall indrawing, cyanosis and mental status (ie, normal, irritable or lethargic) and response (according to alert, response to voice or pain, unconscious (AVPU) scale). Each child’s weight is measured by using an electronic weighing scale with a precision of 0.1 kg; length is measured using a standard-length board with a precision of 0.5 cm and MUAC is measured using a standard MUAC tape with a precision of 0.2 cm by the trained and experienced study nurse of Dhaka hospital. Fever is defined when the axillary temperature is 38°C or greater. Respiratory rate is counted for a full 60 s by exposing the trunk when the child is awake and calm; the presence of lower-chest-wall indrawing is noted at the same time. Oxygen saturation is measured using a portable pulse oximeter (Handheld Vital Signs Monitors-NT1D, Solaris Medical Technology, USA) with a probe on a finger or toe when the child breathes in room air. Oxygen saturation of <90% is defined as hypoxaemia, which is an indication for supplemental oxygen therapy by using BCPAP. Blood group and Rh typing are done at the bedside and we exclude the child having negative blood groups.

Bedside Hb (if not known) is checked by using HemoCue Hb 301 analyser (HemoCue AB, Sweden) during the screening period to exclude severely anaemic children requiring an urgent blood transfusion. The length of ICU stays, the total length of hospitalisation and time-to-achieve-recovery (time required for the restoration of mean arterial pressure (MAP) after the starting of the intervention for fluid refractory shock) are recorded. We are also keeping a record of stool and urine volume. Any deterioration or adverse events (ie, signs of heart failure or need for mechanical ventilation) are also documented. Both the study and outcome are recorded including treatment failure/success, hospital discharge, referrals and deaths or left against medical advice.

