### Sample size

The 2010–2011 data from the ICU of the Dhaka Hospital of the icddr, b (the proposed study site) revealed that among the 36 severely malnourished children with shock, 22 died, that is, mortality rate among SAM children with septic shock was 61% (22/36). We assumed that the proposed interventions would reduce the case fatality rate by 50%, that is, the rate will decrease from 61% to 31%.

To detect this magnitude of difference in the death rate, with 80% power (20% type II error) and 0.05 type I error, the required sample size is 40 children in each of the three groups. Considering around 10% drop-outs after enrolment, the total sample size would be 45 children at least in each of the three groups, that is, a total of 135 children—the final sample size of our study.

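### Comparing need for mechanical ventilation as a plain proportion, with planned mortality of 61% v 31%, can tilt the result against the arm with fewer deaths

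*Protocol article*

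**What the plan says.** All places are in the protocol article.

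- *Outcome measures* lists as secondary outcomes "need for mechanical ventilation, the incidence of heart failure, duration of ICU stay and total hospitalisation, time-to-achieve recovery". It gives no rule for a child who dies without having been ventilated.
- *Data collection, management and analysis* compares categorical variables by χ² or Fisher's exact test and plans intention-to-treat and per-protocol analyses. Kaplan-Meier curves are planned for survival. No composite with death is described.
- *Sample size* assumes that "the rate will decrease from 61% to 31"%, with 45 children per arm after allowance for drop-out.
- *Study intervention and procedure* gives criteria for ventilation: failure of bubble CPAP, judged after at least an hour, or respiratory failure shown by blood gas or by the saturation-to-oxygen ratio.
- *Collection of baseline information* states: "Any deterioration or adverse events (ie, signs of heart failure or need for mechanical ventilation) are also documented".
- Table 1 marks mechanical ventilation in the study-drug, rescue and "Hosp course up to disposal" columns, but not at screening or enrolment.

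**The concern.** Death before ventilation is a competing event. In this trial it is both common and expected to differ between arms. A χ² table over all randomised children has only a yes and a no cell, so unless a rule says otherwise, a child who dies unventilated joins the survivors who never needed a ventilator. The arm with more deaths then has fewer children left to be ventilated and looks better on this outcome. The arm with fewer deaths looks worse, even if the treatments do not differ at all in their effect on breathing.

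The outcome is also one of the two named examples of deterioration or adverse events. If the trial succeeds on its primary outcome, this distortion could be read as a respiratory harm of the better arm.

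**Working it through.** **Inputs from the article.** Case fatality 61% and 31%; 45 children per arm. Expected deaths are 0.61 × 45 = 27.5 and 0.31 × 45 = 14.0.

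**The plan's own figure.** The article sizes mortality only and gives no figure for ventilation. With unpooled variance, two-sided 0.05 (sidedness assumed) and 80% power:

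n = (1.96 + 0.8416)² × (0.61×0.39 + 0.31×0.69) / 0.30² = 39.4, so 40; 40/0.9 = 44.4, so 45.

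The stated 40 and 45 are reproduced. They supply the mortality and the arm size used below and say nothing else on this point.

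**Model 1: competing constant hazards.** Let Hd be the cumulative hazard of death without ventilation and Hm that of ventilation.

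- Higher-mortality arm: Hd = −ln(1 − 0.61) = 0.942
- Lower-mortality arm: Hd = −ln(1 − 0.31) = 0.371
- Hm is assumed equal in both arms, from 0.3 to 1.0. If nobody died, 1 − exp(−Hm) = 26% to 63% would be ventilated.

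Observed ventilation = Hm/(Hm+Hd) × [1 − exp(−(Hm+Hd))].

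Death or ventilation = 1 − exp(−(Hm+Hd)).

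SE of the difference = √[p₁(1−p₁)/45 + p₂(1−p₂)/45].

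| Hm | Ventilated, higher v lower mortality | False excess | SE | Excess/SE | Death or ventilation |
|---|---|---|---|---|---|
| 0.3 | 17.2% v 21.9% | 4.7 points | 8.3 points | 0.56 | 71% v 49% |
| 1.0 | 44.1% v 54.4% | 10.3 points | 10.5 points | 0.98 | 86% v 75% |

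The ventilation hazard is identical by construction, so the whole excess is an artefact of mortality. The composite points in the direction of the true benefit.

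**What model 1 assumes about deaths.** It applies 61% and 31% as the risk of death in children not ventilated. Deaths without ventilation are Hd/(Hm+Hd) × [1 − exp(−(Hm+Hd))]. As a share of all deaths this is 88% and 87% of the two arms' deaths at Hm = 0.3, and 68% and 65% at Hm = 1.0. If instead the death hazard after ventilation is 5 to 10 times higher (assumed) and overall mortality is held at 61% v 31%, the excess is about 4 to 5 points at Hm = 0.3 and about 5 to 7 points at Hm = 1.0.

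**Model 2: shares.** Suppose true need is equal in both arms and a share u of each arm's deaths needed ventilation but died without it and was scored no. The false excess is (0.61 − 0.31) × u = 0.30u: 3 points at u = 10%, 7.5 at 25%, 15 at 50%, and none at u = 0. The direction is the same as in model 1.

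**The case against.** **The scoring is inferred.** No passage says that an unventilated death is a no. The outcome is worded as need, and the article gives criteria, so a child who met them and died first could be counted as needing ventilation. That stands for some deaths only. A child who dies within the first hour of bubble CPAP cannot meet that criterion, and one who dies of circulatory failure may meet no respiratory criterion. These children remain a no on any reading.

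**The size rests on assumptions.** The article gives no ventilation rate. Model 1 places most deaths outside ventilation, although all study children stay in an ICU with ventilators. Mortality is counted to day 28 ± 3, whereas the ventilation row of Table 1 ends at disposal, so deaths after discharge do not compete. All of this stands and pulls towards smaller figures.

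**It may be dealt with elsewhere.** This is a condensed article, and a fuller plan may hold a rule. Deaths will also be reported as the primary outcome. Both are reasons for low priority. The comparison that the article does name still has the weakness described.

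**Stronger readings a reader might infer.**

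- *That the outcome cannot inform at all.* A bias of at most about one standard error in model 1 does not support that.
- *That children already ventilated at entry are counted as events.* Entry is open to children "who develop fluid refractory shock either at admission or at any point during their treatment in the hospital", and the nearest exclusion is "a requirement of cardiopulmonary resuscitation during screening and non-consent from the caregivers/parents", so a ventilated child could be enrolled. But the outcome is recorded as a deterioration and is marked only from study drug onward, which points to new events. No passage says that such children are enrolled or counted. If they were, randomisation would balance them on average, and the effect would be mainly dilution.
- *That incidence of heart failure has the same problem.* No analysis here supports that extension.

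**Conclusion.** The concern holds as a modest weakness of one secondary outcome. With mortality planned at 61% v 31%, a simple proportion compared by χ² or Fisher can be tilted against the arm with fewer deaths. The tilt is about 5 to 10 points (0.6 to 1.0 SE at 45 per arm) if ventilation hazards are equal and most deaths occur without ventilation, and about 4 to 7 points if many deaths follow ventilation. It vanishes if almost no child dies unventilated. The mortality figures and arm size are the article's; the ventilation hazards are assumed. The article does not establish that ventilation at entry is miscounted. The primary outcome is unaffected.

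**What to change.** In the analysis plan:

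1. State that only mechanical ventilation started after randomisation counts as an event.
2. Report death or new mechanical ventilation by arm beside the ventilation proportion.
3. State that the ventilation-alone comparison is read only together with deaths.

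Replacing the proportion by a cumulative incidence with death as competing event would not be enough. With complete follow-up it returns the same proportion.

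The cost is a few sentences and one extra table, since ventilation and death are already recorded and no clinical procedure changes. The downside is that the composite is driven largely by death and overlaps the primary outcome. Its components must therefore be shown separately, and it should not be presented as independent evidence of benefit.
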